## Introduction

Postoperative pulmonary complications (PPCs) include acute respiratory distress syndrome (ARDS), atelectasis, pulmonary oedema, aspiration, and pneumonia, which may lead to persistent lung injury, respiratory distress, and prolonged mechanical ventilation after surgery. Almost all patients undergoing cardiac surgery with cardiopulmonary bypass (CPB) develop some degree of postoperative pulmonary dysfunction, and 10%-25% patients develop PPCs.^1^ Postoperative pulmonary complications significantly worsen prognosis and result in prolonged recovery periods in the intensive care unit (ICU) and length of hospital stay.^2^ Although preoperative chronic obstructive pulmonary disease (COPD), smoking, anaemia, advanced age, and weakness impacted the incidence of PPCs, multiple intraoperative and postoperative factors such as mechanical ventilation, surgical manipulation, CPB, transfusion, lung recruitment manoeuvres, anaesthetic agents, and high-level fraction of inspired oxygen (FiO_2_) have been suggested as potential contributors to lung injury and PPCs.^3^

A postoperative protective or noninvasive mechanical ventilation strategy with low tidal volume [6 mL kg^–1^ ideal body weight (IBW)], lower driving pressures, and positive end-expiratory pressure (PEEP) is widely accepted as a key method for lung protection.^4^ However, intraoperative protective ventilation strategies are inconsistent and controversial during cardiac surgery, which suggests potential confounding factors may account for these results.^5^ Many critically ill cardiac surgical patients receive 1.0 FiO_2_ as a precaution to prevent hypoxia; thus, hyperoxia is common during cardiac surgery with a wide range of oxygen settings. Oxygen can directly and indirectly injure organs in 3 ways: (1) hyperoxia-related cardiovascular dysregulation, such as bradycardia and increasing vascular resistance; (2) direct tissue injury from increased production of reactive oxygen species (ROS); and (3) enhancement of ischaemia–reperfusion injury.^6^ Several clinical studies suggest that hyperoxia can cause myocardial injury, acute kidney injury (AKI), and neurologic dysfunction after cardiac surgery.^6^

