After anaesthesia induction and intubation, the restrictive oxygenation group will have FiO_2_ set at a minimum of 0.3 to maintain SpO_2_ greater than or equal to 95%. If the SpO_2_ is above 95%, a 10% further reduction in FiO_2_ will be attempted to achieve the lowest possible FiO_2_ while maintaining an SpO_2_ > 95%. During CPB, a blended air/oxygen mixture will be titrated to ABG results with the goal of PaO_2_ between 100 and 150 mmHg. The liberal oxygenation group receives 1.0 FiO_2_ throughout the intraoperative period, including during CPB. After admission to ICU, all patients will receive 0.5 FiO_2_ initially and then titrated to the lowest FiO_2_ while maintaining SpO_2_ ≥ 95% until extubation. Criteria for sedation weaning include a stable heart rate and blood pressure and a chest tube output < 200 mL over the last 2 hours. Criteria for mechanical ventilation weaning trial include a rapid shallow breathing index <100, a respiratory rate < 35, an SpO_2_ > 92%, a heart rate < 140 bpm, a systolic blood pressure <180 mmHg and >90mmHg, and no anxiety or diaphoresis from increased work of breathing. Goal-directed extubation criteria will be utilised in the cardiac ICUs of study centres. These criteria include an FiO_2_ ≤ 0.40, an SpO_2_ ≥ 95%, a rapid shallow breathing index < 100, and a negative inspiratory force ≥ –20cm H_2_O. Postoperative narcotic analgesia and sedation approaches are standardised to minimise the discrepancies among the centres. After extubation, the patient may still need continuous oxygen support in the ICU or after ICU discharge, and the lowest SpO_2_/FiO_2_ ratio will be recorded daily until discharge from the hospital.

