### Statistical Analysis

#### Sample Size Calculation

A decrease of 10% in PaO_2_/FiO_2_ from the baseline is considered as clinically significant. The ARDS definition is PaO_2_/FiO_2_ less than 300 mmHg; thus, a difference of 30 mmHg of mean value of the lowest PaO_2_/FiO_2_ postoperatively between the 2 groups will be considered as clinically significant. Assuming SD of 60 mmHg, *α* = 0.05, and 80% power with 2-sided *t*-test, at least 160 subjects will be needed in total to detect a difference (80 patients in each group). Considering potential withdrawal, protocol violation, and failure to follow-up, we will aim to recruit 200 patients (100 patients in each group) for this study.

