### Data Analysis

Data will be expressed as mean ± SD or median (minimum and maximum) and percentage as appropriate for continuous and categorical variables, respectively. A *t-*test will be used to compare continuous variables. For comparison of ratio or ordinal categorical data, the Pearson chi-squared test (or Fisher’s exact) or a Mann–Whitney *U*-test will be used. Two-sided *P-*values less than .05 will be considered statistically significant. All the analyses will be conducted using the R software.

The primary outcome of the study is the lowest PaO_2_/FiO_2_ within 48 hours after ICU admission between liberal and restrictive oxygenation groups. A non-parametric equivalent *t-*test will be used to compare groups. The percentage of shift from baseline will also be calculated and compared by the *t-*test. The ratio of shift over 10% from the baseline of each group will be compared by the chi-squared test. Secondary outcome analysis of PPC incidence and mortality of the groups will be compared by the chi-squared test. Odds ratios or measures of relative risk will include 95% CIs. Secondary outcomes including the length of mechanical ventilation and lengths of postoperative ICU and hospital stay will be calculated and compared by a *t-*test.

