### Secondary Endpoints

The European taskforce published guidelines for perioperative clinical outcomes (EPCO) (Table 3)^12^; PCCs after surgery include ARDS, noncardiogenic pulmonary oedema, pulmonary infection, pneumonia, pleural effusion, atelectasis, and respiratory failure. The composite of these events is considered as the secondary endpoint of this study. Other secondary outcomes will include the duration of mechanical ventilation, ICU and hospital stay, and patient mortality within 7 postoperative days. Time-weighted average of PaO_2_/FiO_2_ ratio within the first 48 hours will also be followed as an additional outcome.

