## Discussion

There are 500 000 cardiac surgeries a year in the USA alone. Almost every patient has lung injury, and up to 25% of them develop PPCs after cardiac surgery.^13^ Most of prior studies focus on postoperative mechanical ventilation strategies and incidence of PPCs and mortality in the ICU.^14,15^ Postoperative pulmonary complications are mainly attributed to ventilation-induced lung injury (VILI) and ventilator-associated pneumonia (VAP). Both VILI and VAP are highly time dependent and are most common in patients who are ventilated for longer than 48 hours postoperatively. A protective mechanical ventilation strategy or an adaptive support ventilation triggered by spontaneous breathing is wildly accepted and applied to wean patients in the ICU.^15, 16^ Nowadays, patients are usually extubated within 6 hours postoperatively after an uneventful CABG. Therefore, the intraoperative mechanical ventilation has become an important proportion of overall mechanical ventilation.^17,18^ Therefore, the intraoperative ventilatory management might have significant impacts on outcomes after CABG even more than the ICU management.

Several studies suggest that a protective ventilation strategy is beneficial and can reduce PPCs, but some studies found no improvement or even increased mortality in cardiac patients with the protective ventilation strategies.^5,19^ The most significant ventilation parameter change between intra- and postoperative period is FiO_2_, and scarce data currently exist to evaluate the relationship between intraoperative FiO_2_ and PPCs in cardiac surgery.

Previous studies on FiO_2_ have diverse definitions of hyperoxia. Some studies’ criteria for hyperoxia are in the normoxia range for other studies.^20^ There are no well-established PaO_2_ targets on CPB, and clinical practice is highly variable. Based on the oxygen haemoglobin dissociation curve of normal subjects, SpO_2_ decrease from 100% to 90% will decrease PaO_2_ by 40 mmHg. We choose a minimum SpO_2_ of 95% as our safe threshold because it is close to PaO_2_ 80mmHg. The PaO_2_ from ABG is more accurate and reliable but cannot be monitored continuously; thus SpO_2_ is a more feasible and appropriate index for FiO_2_ adjustments.

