BMI, body mass index; CABG, coronary artery bypass graft; COPD, chronic obstructive pulmonary disease; CPB, cardiopulmonary bypass; ECMO, extracorporeal membrane oxygenation; ICU, intensive care unit; RBC, red blood cell; VAD, ventricular assist device.

**Table 3. t3-tjar-51-2-112:** Definition of Postoperative Pulmonary Complications

Complications	Definitions or Diagnostic Method
Respiratory infection	Antibiotics for suspected infection with 1 or more of the following: new or changed sputum, new or changed lung opacities, fever, white blood cell count >12 × 109 L^–1^
Atelectasis	Lung opacification with mediastinal shift, hilum or hemidiaphragm shift towards the affected area, with compensatory hyperinflation in adjacent non-atelectatic lung
Pneumonia	Chest x-ray with at least 1 of the following: infiltrate, consolidation, and cavitation, plus at least 1 of the following: fever >38˚C with no other cause, white cell counts 12 × 10^9^ L^–1^, and >70 years of age with altered mental status with no other cause plus at least 2 of the following: new purulent/ changed sputum, increased secretions/suctioning, new/worse cough/dyspnoea/tachypnoea, rales/bronchial breath sounds, and worsening gas exchange
Noncardiogenic pulmonary oedema	Evidence of fluid accumulation in the alveoli with enough cardiac output
Pleural effusion	Chest x-ray with blunting of costophrenic angle, loss of sharp silhouette of the ipsilateral hemidiaphragm in upright position, displacement of adjacent anatomical structures, or (in supine position) hazy opacity in 1 hemithorax with preserved vascular shadows
Respiratory failure	Postoperative PaO_2 _< 60 mm Hg on room air
Acute respiratory distress syndrome	PaO_2_/FiO_2_ ratio < 300 mm Hg

Adapted from Jammer (2015).^12^

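### Table 3 defines ARDS by PaO2/FiO2 below 300 alone, so one component of the PPC composite is the primary outcome cut at 300

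*Protocol article*

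**What the plan says.** In Table 3 the whole entry for ARDS is "PaO_2_/FiO_2_ ratio < 300 mm Hg". It sets no imaging, timing or cause criterion, although the rows for pneumonia, atelectasis and pleural effusion give radiological detail. The Sample Size Calculation section uses the same definition: "The ARDS definition is PaO_2_/FiO_2_ less than 300 mmHg".

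The Secondary Endpoints section lists ARDS with noncardiogenic pulmonary oedema, pulmonary infection, pneumonia, pleural effusion, atelectasis and respiratory failure, and states: "The composite of these events is considered as the secondary endpoint of this study". Table 3 gives respiratory failure as a postoperative PaO2 below 60 mmHg on room air.

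Under Data Analysis, "The primary outcome of the study is the lowest PaO_2_/FiO_2_ within 48 hours after ICU admission". PPC incidence is to be compared by a chi-squared test. The Abstract and Introduction word the trial hypothesis in terms of PPC incidence. For background, the Introduction says that "10%-25% patients develop PPCs" after cardiac surgery with bypass.

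**The concern.** A composite of complications is normally read as clinical evidence that stands beside a physiological primary outcome. Here one component needs nothing except the physiological measurement. A single low ratio among the scheduled ICU blood gases makes a patient a PPC case, with no sign of a complication on film or at the bedside.

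Two consequences follow. The composite rate may be set largely by where the ratio happens to lie relative to 300. A treatment effect on the ratio also passes mechanically into the composite. A report that both the primary outcome and PPC incidence favoured one arm would look like two findings when it could be one. This matters because PPC incidence is the hypothesis that the trial states.

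**Working it through.** **Inputs from the article.** SD 60 mmHg and difference 30 mmHg (Sample Size Calculation: "a difference of 30 mmHg of mean value of the lowest PaO_2_/FiO_2_ postoperatively between the 2 groups will be considered as clinically significant"); ARDS cut 300 mmHg (Table 3); 80 evaluable patients per arm; PPC background 10%-25% (Introduction). The 30 mmHg is 10% of 300. No expected mean of the lowest ratio is given for either arm, so the means below are assumptions.

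**The plan's own figure.** With these inputs the normal formula gives n = 2 × (1.96 + 0.84)² × 60² / 30² ≈ 63 per arm, and the t-test gives 64. The article states 80. The total of 160 equals 128/0.8, so it may already include a 20% loss. The stated size is therefore conservative, and the point here does not depend on it.

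**Step 1: overlap by definition.** If the lowest ratio within 48 hours is below 300, the ARDS row is met and so is the composite. Respiratory failure adds no one beyond that row: a PaO2 below 60 on room air means a ratio below 60/0.21 = 286, which is under 300. The ARDS row has no time limit and Table 1 assesses PPCs up to discharge, so later gases could add cases. The shares below are then a minimum.

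**Step 2: share classified by the ARDS row alone.** Assume the lowest ratio is normal with SD 60. The share below 300 is Φ((300 − mean)/60).

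| Assumed means (higher/lower arm) | Higher arm | Lower arm | Overall |
|---|---|---|---|
| 300/270 | Φ(0) = 50% | Φ(0.5) = 69% | 60% |
| 315/285 | Φ(−0.25) = 40% | Φ(0.25) = 60% | 50% |
| 330/300 | Φ(−0.5) = 31% | Φ(0) = 50% | 40% |
| 360/330 | Φ(−1) = 16% | Φ(−0.5) = 31% | 23% |

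For this row alone to stay at or below 25% overall, the means must be about 357/327 or higher: Φ(−0.95) = 17% and Φ(−0.45) = 33%, average 25%.

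**Step 3: the whole composite.** Assume that the other components affect a share q of patients, independently of the ratio and equally in both arms. The composite rate is 1 − (1 − p)(1 − q), where p is the overall share from Step 2. With q from 10% to 25%, the overall rate is 64%-70% at 300/270, 55%-63% at 315/285, 46%-55% at 330/300 and 31%-43% at 360/330.

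**Step 4: how far a shift in the ratio carries over.** Take a two-proportion test at two-sided 0.05 with 80 per arm.
- ARDS row alone: the planned 30 mmHg shift gives about 70% power at means from 300/270 to 330/300, and 61% at 360/330.
- Composite with q of 10%-25% and no effect on the other components: it still reaches significance about 45%-62% of the time at means from 300/270 to 330/300, and about 30%-45% at 360/330.

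**A boundary illustration.** The Discussion chooses SpO2 95% "because it is close to PaO_2_ 80mmHg". A patient exactly at that saturation on FiO2 0.40, the two oxygenation limits in the extubation criteria, has a ratio of 80/0.40 = 200. Such a patient meets those two limits and is also an ARDS case under Table 3.

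**The case against.** The strongest reply is that Data Collection says complications will be diagnosed by the EPCO definitions, with trained, blinded assessors and interrater checks, and that Table 3 is marked as adapted in a condensed article. Fuller criteria may therefore apply in practice. This does not cure the row. The Secondary Endpoints section points to Table 3 for those definitions, and the Sample Size Calculation section repeats the ratio-only version. If fuller criteria are meant, assessors have two sources that may differ.

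Other parts of the reply stand:
- A reader might infer that half or more of patients meet the composite on the plan's own numbers. The plan fixes only the SD and the difference. It uses 300 as a threshold and as the lower edge of normal, not as an expected mean. From this row alone, half overall needs means of about 315/285 or lower.
- A reader might infer that the whole composite repeats the primary outcome. Only ARDS does, with respiratory failure nested in it. The other five components are clinical or radiological. The article gives no rates for them, so they cannot be said to add little.
- Nothing in the article says that ratios below 300 are normal after CABG. The Primary Endpoint section puts normal above 300.
- The 80/0.40 example is a limiting case. Nothing says that patients sit at both limits together.
- The 10%-25% is a background figure and not a planning assumption.

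**Conclusion.** The concern holds for the ARDS component. As printed, it is a dichotomised copy of the primary outcome and contains the respiratory failure component. This follows from the definitions and needs no assumption.

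The size is conditional. With SD 60, arms 30 mmHg apart and a normal distribution, the row alone classifies about 40%-60% of patients if the means lie near 300 (330/300 down to 300/270), and 23% at 360/330. It exceeds the top of the cited 10%-25% range unless the means are about 357/327 or higher. The composite rates and the carry-over in Step 4 also assume that the other components are independent of the ratio and equal between arms.

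This is a should-fix point. The composite is a secondary endpoint, and the primary outcome, its test and the sample size are unaffected. It still deserves correction, because the composite is the direct test of the stated hypothesis.

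**What to change.** 1. Reconcile the ARDS row of Table 3, and the matching sentence under Sample Size Calculation, with the full definition in the EPCO source that the article cites, so that the ratio alone does not make a case. Blinded assessors would judge it from imaging already obtained.
2. Report the proportion of patients with lowest PaO2/FiO2 below 300 as a separate descriptive outcome.
3. Pre-specify, as a supporting analysis, the PPC composite without the ratio-only gas-exchange components (ARDS as printed, and respiratory failure).

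Cost: a change to the definition and the case report form, plus one further analysis. The article says that recruitment has not begun, so no collected data would need to be reclassified. The composite event rate will fall, and power for it with it. Only the ICU-admission chest x-ray is scheduled, so any imaging criterion that needs a later film will depend on films taken for care, and case finding will partly follow clinical indication. The report should state this limitation.
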